### Sample size calculation

The primary endpoint of this study was the mean number of symptom threshold events, which is calculated by averaging the number of target symptom threshold events per patient at each time point. The minimum important difference (MID) has been defined as the smallest difference in the scores of the PRO measure that patients perceive as beneficial or harmful and would lead the clinician to consider a change in treatment. The literature recommended that the minimum difference between the two groups should be ≥ 0.3 sd based on the clinical treatment comparison efficacy measured by PRO instruments [31]. To meet the MID (0.3 sd) with the PRO instrument for mean symptom threshold events, the sample size required for each group was 176 when rejecting the null hypothesis (difference between the two groups < 0.3 SD). A total of 352 samples are required in this study. According to the previous pre-investigation experience, the loss rate of follow-up and withdrawal was 20%; 220 patients should be the adequate number of participating patients for each group (176/0.8). Because this trial is an intervention study, the follow-up time is 3 months after major lung operations. The sample size calculation is based on the independent sample Student’s *t*-test, using a two-tailed test (*α* = 0.05, 1 − *β* = 0.8).

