**Clinical characteristics**									
Surgical procedure, surgical approach, extent of surgery, stage, postoperative length of stay, postoperative chemotherapy									

Interventions are based on participants’ ePRO scores, and if there is a target symptom score ≥ 4, there will be corresponding treatment

The adherence to the intervention measures will be evaluated at every given time. If the participants fail to comply with the intervention measures as required more than two times, it will be considered a severe violation of the study protocol and removed from the trial. If the participants have serious complications after the operation and cannot complete the PRO questionnaire with poor compliance or deliberately miss the questionnaire filling or request to withdraw, they will be stopped from further collecting the relevant data.

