### Statistical analysis

The primary and secondary outcomes will be analyzed based on the protocol set. To be included in the analyses, a participant must provide MDASI-LC data from the baseline and at least two additional time points, QLQ-C30 data from the baseline, and at least one postoperative time point. All outcomes will also be analyzed based on full analysis set. The analysis will be carried out on the thoroughly collected data with the definition of statistical significance as *P* ≤ 0.05. Classification variables will be expressed in frequency or proportion and compared between groups with the *χ*^2^ test. Continuous variables will be represented by $$\overline{x}\pm s$$ or *M*(*P*_25_, *P*_75_) and compared between groups using Student’s test or Wilcoxon rank sum test. The changes in PROs in the intervention and control groups will be compared using the generalized mixed-effect model. Missing data will be processed by multiple interpolations. Subgroup analysis of patients undergoing postoperative chemotherapy. Sensitivity analysis is mainly to compare the data without missing data to the data set with multiple imputed data.

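### The one named missing-data sensitivity analysis compares two methods that both assume ignorable missingness, so it cannot detect the informative dropout that the protocol's own stopping and removal rules make plausible

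*Protocol article*

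**What the plan says.** The Statistical analysis section of the protocol article gives the main method as "Missing data will be processed by multiple interpolations" (multiple imputation is evidently meant) and the check on it as "Sensitivity analysis is mainly to compare the data without missing data to the data set with multiple imputed data". It states no assumption about why data are missing, and it names no analysis that departs from missing at random.

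The primary analysis uses the protocol set. To enter the analyses, "a participant must provide MDASI-LC data from the baseline and at least two additional time points", with a parallel requirement for the QLQ-C30. The section adds: "All outcomes will also be analyzed based on full analysis set".

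The text after Table 1 sets out how data come to be missing. It begins "If the participants have serious complications after the operation and cannot complete the PRO questionnaire", goes on to deliberately missed forms and requests to withdraw, and concludes that "they will be stopped from further collecting the relevant data". The same paragraph removes from the trial participants who fail to follow the intervention measures more than twice. The Sample size calculation section plans on the basis that "the loss rate of follow-up and withdrawal was 20" per cent.

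**The concern.** A missing-data sensitivity analysis should change the assumption that the main analysis cannot verify. Here the main analysis assumes that, given the observed data, missingness does not depend on the unseen scores. The comparator, complete data only, generally relies on a stricter version of that assumption. Neither allows a patient to be missing because the unrecorded symptoms were bad.

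That is the mechanism the protocol's rules suggest. Complications, poor compliance and withdrawal are plausibly linked to symptom burden, and symptom threshold events are the primary outcome. The mechanism may also differ by arm. The Control group section says controls receive no specific symptom guidance, so removal for failing the intervention measures falls mainly on the intervention arm. The trial is open-label as well.

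At stake is the robustness claim. If sicker intervention patients drop out, both analyses can be biased in the same direction by similar amounts, and their agreement would then be read as reassurance.

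**Working it through.** **1. The plan's own figures.** Inputs from Sample size calculation: 0.3 SD, two-sided alpha 0.05, power 0.80, 20% loss. By the normal approximation, n = 2 × (1.960 + 0.842)² / 0.3² = 174.4, so 175 per group. The t-based solution is 175.4, so 176. Then 176 / 0.8 = 220 per group, 440 in total. The stated sample size reproduces.

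**2. How much may be imputed.** Table 1 lists 15 post-operative MDASI-LC visits (days 1, 3, 5, 7, 14, 22, 29, 36, 43, 50, 57, 64, 71, 78, 86). The text implies 4 + 12 = 16. A patient with baseline and two later forms meets the MDASI-LC entry rule, so up to 15 − 2 = 13 of 15 forms could be imputed for that patient.

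**3. Size of a bias that the comparison would miss.** Suppose a fraction f of the intervention arm is wholly imputed and is truly δ SD worse than imputed, with controls imputed correctly. The benefit is then overstated by f × δ. With f = 0.20 (the stated loss rate) and δ assumed:
- δ = 0.5: 0.20 × 0.5 = 0.10 SD, one third of the 0.30 SD target.
- δ = 1.0: 0.20 × 1.0 = 0.20 SD, two thirds of the target.

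These are upper-end figures, because patients who stop early still contribute the forms they completed.

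**4. Would the two methods disagree and so give a warning?** An illustrative simulation used assumed inputs: no true effect; 220 per arm; outcome SD 1 with higher values worse; a baseline covariate correlated 0.5 with the outcome; and 20% missing in each arm. Missingness was random in controls and more likely with worse outcomes in the intervention arm. Over 400 runs with five imputations each, the mean difference (intervention minus control) was:
- full data: 0.00 SD
- complete cases: −0.19 SD
- multiple imputation: −0.15 SD

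Both methods show a benefit that does not exist, and they lie 0.04 SD apart.

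**5. How many patients the complete-data analysis keeps.** The article does not define complete data and gives no per-form completion rate. If it means every post-operative form, and forms are missed independently with completion probability p (assumed), the share kept is p^k:

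| p | k = 15: share (of 440) | Power at 0.3 SD | k = 16: share |
|---|---|---|---|
| 0.95 | 46% (204) | 0.57 | 44% |
| 0.90 | 21% (91) | 0.30 | 19% |
| 0.85 | 9% (38) | 0.15 | 7% |

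If missingness clusters by patient (beta-binomial, within-patient correlation 0.1 to 0.7, 15 forms), the share is 63% to 90% at p = 0.95 and 39% to 80% at p = 0.90. If the stated 20% is the only loss, it is 80%, or 352 patients, which is the planned evaluable number.

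**The case against.** The strongest reply is that this is mostly an omission. The article says the sensitivity analysis is mainly this comparison, which leaves room for others. Delta-adjusted analyses and imputation details commonly sit in a statistical analysis plan, which is not shown. Comparing complete with imputed data is also conventional. Part of this stands: a reader might infer that no other sensitivity analysis is planned, and the wording does not support that. What does not fall away is that the method stated here cannot test the main threat. The additional full-analysis-set run changes who is analysed, not the missingness assumption.

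A reader might also infer that the complete-data analysis would keep only a small fraction of patients. The documents do not establish this. It needs completion of about 90% or less per form with near-independent gaps, whereas the stopping rules suggest whole-patient dropout, which clusters. The Data collection section describes reminders, calls and assisted completion. If the primary outcome counts only forms after discharge, about 11 forms (Table 1) matter, and 0.95^11 = 57% or 0.90^11 = 31% would be kept.

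A third inference is that "The analysis will be carried out on the thoroughly collected data" contradicts imputation. It is awkward wording that may simply mean analysis after collection is finished, and the same section plainly provides for imputation.

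Nor would disagreement between the two analyses be useless, since it would suggest that complete cases are unrepresentative. Finally, the bias figures assume a one-arm shift whose size no document supports, and patients left out of the protocol set are not imputed there at all. That is why the figures are only an illustration.

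**Conclusion.** The point holds in a limited form. The one named missing-data sensitivity analysis sets two ignorable-missingness approaches side by side and cannot detect informative dropout, including dropout that differs by arm. The protocol's rules for ending data collection and removing patients make such dropout plausible, and 20% loss is expected.

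The possible overstatement of benefit is 0.10 to 0.20 SD against a 0.30 SD target. This assumes that 20% of the intervention arm is wholly imputed and truly 0.5 to 1.0 SD worse than imputed, so it is an upper-end illustration and not an estimate. The precision of the complete-data comparison is unknown and should be given only as a range under stated assumptions.

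The choice of multiple imputation for the main analysis is not in question. The change is worth making because the robustness claim would otherwise be unsupported against the bias that matters most.

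**What to change.** Keep multiple imputation as the main method, and keep the complete-data comparison as a descriptive analysis with complete data defined and the number of patients retained reported by arm.

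Add one pre-specified departure from missing at random: delta-adjusted imputation that worsens imputed intervention-arm values in steps up to 1 SD, leaves imputed control values unshifted, and reports the tipping point at which the conclusion changes. Run it on the full analysis set, because patients left out of the protocol set are not imputed there and a shift applied in that set would not reach them.

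The cost is a little more programming and some analysis-plan wording; no further patients, visits or data are needed. The downside is that the conclusion may look less robust.

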## Results and measurements

### Primary outcomes

The main PRO tools in this study include MDASI-LC and EORTC QLQ-C30. MDASI-LC covers 16 lung cancer- and treatment-related symptoms as well as six disturbances to everyday life caused by symptoms and can be completed in five minutes. All items were scored on a scale of 0–10, with 0 as “no symptoms” or “no impact on life” and 10 as “the most serious level” or “complete impact on life.” Besides, the patients can have 24 h as the recall period before filling in MDASI-LC. Comparably, EORTC QLQ-C30 lays out 30 items, incorporating five functional dimensions, three symptom dimensions, six single symptom dimensions, and two total health status items. These can be done in 5 to 8 min with a recall period of 1 week. EORTC QLQ-C30 scores items 1–27 by the range of 1–4 points, with 1 as “no symptoms” or “no impact on life” and 4 as “the most serious level” or “complete impact on life.” Additionally, items 28 and 29 focus on health status assessment and can be scored by 1 to 7, with 1 as very poor and 7 as very good. For the evaluation, the severity of symptoms and function deterioration increases along the increments of the scores. Conversely, the higher the health score, the better the quality of life. Both scales have been widely used in China’s clinical setting with good reliability and validity [39, 40]. The main measurement indicators and follow-up schedule are shown in Table 1. The primary outcome of this study is the mean number of target symptom threshold events with discharge 12 weeks, which include pain, cough, fatigue, sleep disorders, shortness of breath, sadness and distress. According to published literature, patients with a symptom score of 4–6 can be classified as moderate and ≥ 7 as severe [33]. Thus, we presented the score of 4 as the threshold for intervention and the targeted symptom score of ≥ 4 as a threshold event in this trial. A score of 1 can be given if one of the target symptoms is recorded to be ≥ 4 in one follow-up and 3 if three target symptoms are graded as ≥ 4.

### Secondary outcomes

The secondary outcomes of this study include the changes in PROs (symptom severity, daily function, and quality of life) and follow-up rates after discharge. The trajectory for PROs is defined as the average score of symptom severity for seven targeted symptoms and the average score of six MDASI-LC daily functional intervention items from baseline to 12 weeks after discharge. The trajectory for quality of life comes from the quality of life scale (EORTC QLQ-C30), including the measurement results at baseline and the 4th and 12th weeks after discharge.

### Other data

The specialist workload, the acceptability of the trial interventions, and the satisfaction of patients will be assessed through surveys and interviews. Experts’ workload is mainly determined by the average amount of time spent on each patient’s work through interviews, while experts assess the number of patients managed within a particular time. The acceptability and satisfaction of patients are mainly investigated through questionnaires, including the convenience and satisfaction of using WeChat mini-programs and satisfaction with expert postoperative guidance, among others. Demographic and clinicopathological features, follow-up information, and adverse events of interventions will also be obtained. All adverse events will be evaluated and managed by the thoracic surgeon.

### Patient and public participation statement

Researchers carried out the design, recruitment, and implementation of this study. All the participants are prevented from obtaining the research plan and the results from the ongoing trial. The participants can obtain the final results of this study through our future articles.

### Ethics and communication

All recruited patients must sign the written informed consent for the trial participation before the trial starts. Any subsequent amendments to the protocol will be submitted for further review and approval. The sub-center qualification will be approved and accredited by the hospital-specific ethics committee.

### Data collection, management, and quality control

All participants will be recognized only by their subject ID. MDASI-LC data will be gathered into digital questionnaires through the WeChat applet, which will then be connected to the REDCap platform [41]. The collected paper questionnaire data will be entered into the RedCap platform online by the research assistant of each center. The data of this study adopts the REDCap data collection and management platform built by Xi’an Jiaotong University. All the information of participants will be kept strictly confidential and will be accessed only by members of the trial team or ethics committee. Data in paper files and from WeChat applet will be safely stored in online REDCap and inspected by a third party who is not involved in this study. All the participants will be blinded from obtaining the research plan and the results from the ongoing trial. All the participating patients will take on the WeChat platform to fill in the MDASI-LC questionnaire through an applet designed for this trial. To ensure the accuracy of the data, every participant receives training on how to use the procedure before formal filling. Participants will usually fill in electronic and paper questionnaires by themselves. If participants without smartphones or not using WeChat be addressed, or encounter difficulties filling out the electronic questionnaire, they will be assisted by a data collection staff or their family members who are familiar with the platform and applet to complete the questionnaire. During hospitalization, each patient receives a bedside reminder (one day after the operation) and an electronic reminder twice daily to fill in the MDASI-LC on the scheduled date. After discharge, if the participating patient does not fill in the MDASI-LC by 20 o’clock, they will be personally reminded through the phone or WeChat call by the project management personnel. The paper questionnaires of EORTC QLQ-C30 will be filled by the participants, while other diagnosis-related information will be manually collected and filled in paper table by the trial staff; then, those data will be entered into RedCap. All data on the paper questionnaire will be repeatedly checked by the data entry clerk before and after data are input into the Redcap. All the data will then be checked by the outcome assessors for any errors and missing values before analysis. Each participant in data management and participating doctors have signed a data confidentiality agreement.

### Data monitoring and interim analysis

A data monitoring committee (DMC) will be established on a panel of a clinician, a statistician, and the secretary of the Tangdu ethics committee. DMC members will regularly and independently monitor the safety, validity, and integrity of the randomized parallel control study once every 3 months. DMC will meet twice a year or more if needed. No interim analysis will be conducted because this trial is low-risk and short-term.

## Discussion

This study focused on managing early, medium, and long-term postoperative symptoms after lung cancer surgery. The potential impacts of the findings from this trial possibly include the following: (1) determining whether the PRO-based physiological and psychological symptom management is superior to routine management and whether it is superior to people who only carry out physiological symptom management, (2) determining whether active physiological and psychological symptom management can effectively reduce the burden of symptoms and improve the quality of life of the patients with major lung surgeries, (3) to establish a foundation for future research on whether long-term postoperative symptom management (physiological and psychological symptoms) can improve the survival rate, (4) to investigate whether the postoperative management of lung cancer patients based on WeChat and the intervention of psychiatrists is feasible and acceptable in the actual clinical practice in China, (5) to open a niche for the research on the necessity of psychiatrists in the management of lung cancer patients’ symptoms. The psychological and emotional changes of cancer patients may profoundly affect the prognosis and quality of life of patients. Through the WeChat or phone-based (Fig. 3) guidance, this study has been anticipated to effectively relieve the physiological and psychological pressures on patients, facilitate doctor-patient communication, and provide a new approach for the follow-up and guidance of future lung cancer patients in managing postoperative symptoms.

**Fig. 3 Fig3:**
[figure not shown]
**a** Pop-up window of participant questionnaire filling and standardized symptom management opinions of intervention group (English and Chinese versions). **b** Participant management and interaction window (English and Chinese versions)

This experiment has some limitations. First, the trial will be conducted in China’s well-resourced tertiary hospitals with the participation of psychiatrists, which limits the versatility of hospitals that lack psychologists. Second, the inclusion and exclusion criteria are stringent. For example, patients who do not use smartphones may be excluded, resulting in selection bias. Third, the participating patients and specialists who provide interventions cannot be blinded, leading to measurement bias. Fourth, the patients may take more than 15 min to complete the questionnaire, increasing the burden on patients.

### Strengths and limitations of this study

This multicenter randomized controlled trial will be conducted in four tertiary hospitals in China, comparing the effects of patient-reported versus standard postoperative symptom management in patients with lung cancer. In patient-reported management, the lung cancer-specific scale MDASI-LC will be integrated into an online questionnaire survey in the early, medium, and long-term management after the operation, which covers the clinical information of preoperative baseline, postoperative hospitalization, 1, 3, 5, and 7 days after the operation, and once a week after discharge until 12 weeks. Moreover, EORTC QLQ-C30 was used to investigate the quality of life at baseline and 4 and 12 weeks after the operation. Various postoperative adverse events or clinical issues of the patients will be instantly managed through the WeChat platform. Essentially, this trial will monitor and manage the physiological symptoms of the disease and the emotional symptoms of the patients. However, due to the demand for the participation of psychiatrists in this new caregiving model, the methodology and outcome of this trial may be limited by the promotion and application of some hospitals.

In conclusion, as a randomized controlled trial, this study will test the feasibility of the symptom management system based on the WeChat applet in postoperative caregiving and the efficacy of psychiatrist-assisted treatment and provide evidence in managing patients’ symptoms in the medium and long term.

## Trial status

The study began recruitment on 20 April 2022 and will continue until the last patient’s visit (anticipated 30 June 2023). Current protocol: version 1.2 (20.08.2021). Trial registration number: ChiCTR 2200058876, Registered 18 April 2022. The name of the registry is Chinese Clinical Trial Registry and the URL of the trial registry record is https://www.chictr.org.cn/.

## Data Availability

The raw data are available upon reasonable requests to the corresponding authors.

## Abbreviations

QOL: Quality of life
PRO: Patient-reported outcome
RCT: Randomized controlled trial
MDASI-LC: MD Anderson symptom inventory for lung cancer
EORTC QLQ-C30: EORTC core quality of life questionnaire
ECOG: Eastern cooperative oncology group
MID: Minimum important difference
SOP: Standard operating procedure
DMC: Data monitoring committee
CCI: Charlson comorbidity index
